### Interventions

The study protocol is illustrated in Fig. 2. All participants who fulfil the inclusion criteria will be assessed. This research protocol conforms to the CONTORT 2010 guidance, adheres to the Revised Standards for Reporting Intervention trials (SPIRIT) protocols, and satisfies the SPIRIT checklist criteria (online supplementary additional file 2) [27]. This trial will investigate the TBMT versus a control intervention and accords with the SPIRIT Figure (Table 2). Patients will be randomized to a conventional and task-based mirror treatment group for 5 consecutive days per week for 4 weeks, ensuring a total of 40 min of treatment time per day for each group. A trained and professional occupational therapist will be assigned to conduct this trial, and each patient will sign an informed consent form (online supplementary additional file 1) before treatment.

**Fig. 2 Fig2:**
[figure not shown]
Proposed participant flow

**Table 2 Tab2:**
[figure not shown]
Schedule of enrollment, intervention, and assessment

### Control group (CG)

Depending on the patient’s condition, 20 min of occupational therapy without the mirror will be conducted alongside 20 min of conventional treatment, resulting in a total duration of 40 min. The above training will be performed unassisted by a mirror therapy rehabilitator 5 days a week for 4 weeks.

### Task-based mirror therapy (TBMT)

Patients in the TBMT group will receive 20 min of conventional therapy followed by 20 min of TBMT. We designed an ergonomic mirror therapy device (patent number: Z120212 2278905.3) (Fig. 3). Patients will be seated facing the mirror device, with both hands in the box under the screen that substitutes the conventional mirror. The high-definition LCD can display the mirrored image of the healthy hand. Both hands can move freely in the box. By looking at the image on the LCD screen, the patient may create an “optical illusion” that activates mirror neurons and triggers the active activity of the affected hand. The task orientation is as follows: the patient moves with the healthy limb while observing the mirror image and using the affected hand as much as possible to perform the following movements together: elbow flexion and extension, ulnar and radial deviation, wrist flexion and extension, finger flexion and extension, finger adduction, and abduction, as well as the use of sponge balls, water cups, rags, chopsticks, cups, tubes, and wooden blocks. Patients will use their healthy upper limbs to move objects such as watches and rings to promote imagination. This process focuses on placing an object on the affected limb while exercising on the healthy side to facilitate stimulation. The affected upper limb may not have any allowed voluntary activity [14].

**Fig. 3 Fig3:**
[figure not shown]
Ergonomic mirror therapy device

Appropriate care is permitted during the trial period, including pain management, defecation assistance, and posture management. Hand function interventions are prohibited during non-treatment periods to ensure the effectiveness of the trial.

### Outcome measurements

Patients will undergo clinical outcome measurements at baseline, 4 weeks into treatment, and immediately after 12 weeks of treatment. Evaluations will encompass basic information, indicators of hand function, daily activity, and imaging techniques (DTI, CST integrity assessment, including FA, rFA, ROI, and FC values). Specialized training will be provided to evaluators to ensure the credibility of the evaluation.

#### Primary outcomes

The Fugl-Meyer Assessment for upper extremity (FMA-UE) will be utilized to evaluate the level of upper limb motor function impairment, with a maximum score of 66 points [28, 29]. This assessment includes 23 different movements grouped into four categories (shoulder/elbow/forearm, wrist, hand/finger, and coordination), whereby 33 items are assessed. Rated on a 3-point scale, task completion is scored as 0 for inability, 1 for partial ability, and 2 for near-normal ability. The reliability, validity, and responsiveness of the FMA-UE assessment for stroke patients are well recognized [30]. Therefore, FMA-UE will be considered as the primary outcome.

#### Secondary outcomes

Brunnstrom is a motor function and muscle spasticity assessment method for the affected upper extremity [31]. It includes six stages: Grade 1: absence of random movement, no upper or lower extremity movement; Grade 2: joint response, comovement, and minimal random movements; Grade 3: random comovement with the ability to grasp but not extend; Grade 4: separation of movement, including the ability to pinch and make minor extensions; Grade 5: gradual restoration of muscle tone with fine movements, simultaneous yet independent extension of fingers; and Grade 6: motor ability approaching normalcy but speed and accuracy are suboptimal.

The Modified Barthel Index (MBI) assesses the mobility of stroke patients concerning their ability to carry out specific activities of daily living. These activities include eating, bathing, dressing, bowel and urinary control, toileting, bed and chair transfer, level walking, and stair walking [32, 33]. A total score of 100 can be achieved, and scores of 60 or higher indicate self-sufficiency. Independence positively correlates with the score.

We commonly use the Action Research Arm Test (ARAT) to assess the ability of the affected upper extremity and hand to handle objects of different sizes, weights, and shapes. The test assesses 19 tests of arm motor function, both distal and proximal. Each test is given a score of 0, 1, 2, or 3, with higher scores resulting in better function. The total ARAT score is the sum of the 19 tests, resulting in a maximum score of 57 [34]. Nine Hole Peg Test (9HPT): assesses the patient’s whole hand dexterity. The assessment requires the patient to take nine pegs from the container and insert them into a small pegboard, then remove and place them back into the container. The patient’s score depends on the speed of insertion and removal, with the faster the time, the higher the score [35].

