### Participants

Fifty eligible patients with upper limb motor dysfunction in stroke will be recruited from the outpatient and inpatient departments of the Department of Rehabilitation Medicine, Department of Neurology, and Department of Neurosurgery of the Second Hospital of Chongqing Medical University. Eligible patients had to satisfy the inclusion, exclusion criteria, and termination criteria (Table 1). Information about this trial will be posted via posters in the waiting area of the Rehabilitation Department and the Rehabilitation Medicine Clinic so that interested patients can contact the program director through their therapist. If an applicant meets the study criteria, then they will be invited to participate

**Table 1 Tab1:** Inclusion, exclusion criteria and termination criteria

**Inclusion criteria** 1. Meet the diagnostic criteria for stroke (including cerebral hemorrhage and cerebral infarction) formulated by the 4th National Cerebrovascular Disease Conference in 1995and confirmed by head CT or MRI, and the course of the stroke is 1 to 6 months 2. Abnormal hand function after stroke, Brunnstrom stage I-III, upper limb FMA-UE score lower than 47 3. The contralateral hand is in good condition 4. The age of the patient is 20-80 years old, and the gender is not limited 5. No progressive stroke performance, stable vital signs 6. Cognitive function is relatively intact, MMSE>17 or MoCA>24 7. Be able to follow the clinical treatment plan and sign the subject's informed consent
**Exclusion criteria** 1. Subjects with upper limb dysfunction before stroke 2. Subjects with visual impairment or unilateral neglect 3. Severe cognitive impairment or poststroke depression 4. Metal implants in the body, such as cardiac pacemakers and other metal devices 5. Suffering from serious underlying diseases, such as heart function level 4 (NYHA) or severe COPD 6. Subjects participating in other clinical trials at the same time 7. Subjects judged to be unsuitable for this trial, and withdrawing voluntarily 8. Subjects unable to undergo MRI scans
**Termination criteria** 1. Subjects have serious adverse events or adverse reactions 2. Subjects have other changes in their condition and cannot continue the trial 3. Subjects have significant problems in the design of the protocol or the trial and are unable to determine the efficacy

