### Statistical analysis

Data management and analysis will be conducted in SPSS version 23. Groups will be compared at baseline using the *t* test for independent samples for the continuous variables, and the chi-square test for categorical data. The differences of the outcomes, including the FMA-UE, MBI, ARAT, and the 9HPT, between the groups at each of the trial time points will be analyzed using mixed-design 2-way repeated-measures analysis of variance (ANOVA), taking time (4 levels: preintervention, after 2 weeks, after 4 weeks of intervention and 3 months at the end of the trial for follow-up) as the within-subject factor and group (2 levels: TBMT and CG) as the between-subject factor. If participants drop out during the intervention period, they will not be excluded due to the principle of intention to treat (ITT). Furthermore, in instances of missing data, the continuation of observations (LOCF) method will be employed, whereby the last recorded observation preceding the gap in data will serve as a substitute. Unfavorable stroke outcomes correspond to lower FA values for corticospinal tracts, while robust functional recovery denotes elevated FA values. Subgroup analyses of FA values will be conducted based on the interquartile spacing (< 25% interval; 25–75% interval; > 75% interval) method post the inclusion of all individuals to standardize the baseline conditions of the patients. We will use linear regression model outcomes at 4 weeks post-treatment cessation as the dependent variable (FMA-UE). This model will include treatment assignment (TBMT vs. CT) and baseline outcome measure as fixed-effects, as well as patient characteristics (low or high impairment severity at baseline). We will examine differential impacts by fitting separate models with treatment-impairment severity. We will report relevant point estimates and standard errors for these models and conduct 5% level tests for interaction terms with two-sided alternative hypotheses. A *p*-value < 0.05 is deemed a statistically significant discrepancy.

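### Nearly all enrolled patients are likely to be unscorable or at floor on the 9HPT at baseline, yet it is analysed by a repeated-measures ANOVA with a preintervention level

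*Protocol article*

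**What the plan says.** **Who is enrolled.** Participants, Table 1, inclusion criterion 2: "Abnormal hand function after stroke, Brunnstrom stage I-III, upper limb FMA-UE score lower than 47".

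**What those stages mean.** Secondary outcomes defines the best stage allowed at entry as "Grade 3: random comovement with the ability to grasp but not extend". The next stage, which is outside the entry range, is "Grade 4: separation of movement, including the ability to pinch and make minor extensions".

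**What the test asks.** The same section says of the 9HPT: "The assessment requires the patient to take nine pegs from the container and insert them into a small pegboard". The patient then takes the pegs out and returns them. On scoring, the patient's "score depends on the speed of insertion and removal, with the faster the time, the higher the score". The article gives neither a unit nor a value for inability.

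**How it is analysed.** Statistical analysis covers "The differences of the outcomes, including the FMA-UE, MBI, ARAT, and the 9HPT" with one mixed-design repeated-measures ANOVA. Group is the between-subject factor. Time has four levels: before the intervention, 2 weeks, 4 weeks and the three-month follow-up. The software is SPSS 23. Drop-outs are kept under intention to treat, and gaps are filled with the last earlier observation (LOCF).

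**The concern.** Population, instrument and model are each stated, and they do not fit together. Handling nine small pegs needs pinch and release. The protocol's own grading gives neither to a Grade 3 hand, and Grades 1 and 2 have less function still. The baseline level of the ANOVA is therefore likely to hold either very few times or almost nothing but a floor value.

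The other measures in that ANOVA do not share the problem in this form. The FMA-UE scores inability as 0 on each item, and each ARAT item starts at 0. The 9HPT is the only timed measure in the model.

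At stake is the trial's evidence on manual dexterity, for which the Discussion names the 9HPT.

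**Working it through.** **1. The plan's own figure.** The article gives no sample size or effect for the 9HPT. Its only figure is for the FMA-UE: d = 1.13, alpha 0.05, power 0.95, 44 patients. With n per arm, a two-sided t test has noncentrality d·√(n/2). At n = 22 this is 1.13 × √11 = 3.75 and power is 0.956, so 44 reproduces. It does not bear on the 9HPT, but it supplies a generous effect size for step 3.

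**2. Stage against task.**

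| Item | Protocol text | Consequence |
|---|---|---|
| Best stage at entry | "random comovement with the ability to grasp but not extend" | no pinch or release listed |
| First stage with pinch and some extension | Grade 4 | outside entry criterion |
| 9HPT | take, insert, remove, return nine pegs | needs pinch and release |
| Score | speed | no stated value for inability |
| ANOVA | four levels, preintervention included | needs a baseline value |

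By these definitions the share able to complete the test at baseline should be small. The actual share is not in the documents, so a range is used below.

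**3. If inability is treated as missing.** Repeated-measures ANOVA in SPSS deletes listwise, so a patient with no baseline time is lost at every level. LOCF needs an earlier value, and nothing precedes baseline. Let s be the assumed share scorable at all four levels. Patients left = 50·s. The power shown is for a simple two-arm t test at n = 25·s per arm and d = 1.13, borrowed from the FMA-UE. It shows scale only and is not the power of the planned ANOVA.

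| Assumed s | Patients left | Power at d = 1.13 |
|---|---|---|
| 0% | 0 | none |
| 5% | 2 to 3 | not computed |
| 10% | 5 | 0.15 |
| 20% | 10 | 0.35 |
| 30% | 15 | 0.53 |
| 50% | 25 | 0.77 |
| 100% | 50 | 0.97 |

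For example, s = 20% gives n = 5 per arm, noncentrality 1.13 × √2.5 = 1.79 and power 0.35. The 10% row uses a notional 2.5 per arm.

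**4. If inability is scored as zero speed.** All 50 patients have data. If a share p can do the test at baseline, 50·(1 − p) sit exactly at zero: 45 patients if p = 10%, all 50 if p = 0. Baseline variance is then close to nil.

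At a later visit, let q be the share able, and m and v the mean and variance of their speeds. The visit mean is q·m and the variance is q·v + q(1 − q)·m². A difference in means therefore blends how many patients can do the test with how fast they are. The variance is far from that at baseline, whereas the ANOVA assumes roughly normal scores and a stable variance structure across levels.

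The floor may persist. Assume normal latent ability, a true shift of 1.13 SD, and completion thresholds of 1, 0.5 and 0 SD above the control mean. The shares able are then:

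| Threshold | Able, control | Able, TBMT | At zero, control (of 25) | At zero, TBMT (of 25) |
|---|---|---|---|---|
| 1 SD | 16% | 55% | 84%, about 21 | 45%, about 11 |
| 0.5 SD | 31% | 74% | 69%, about 17 | 26%, about 6 to 7 |
| 0 SD | 50% | 87% | 50%, about 12 to 13 | 13%, about 3 |

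The last two columns are 1 minus the share able, times 25.

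**The case against.** The strongest reply is that a speed score on which higher is better has a natural zero for inability. On that reading nobody is missing. The coding of inability may also sit in the full protocol, analysis plan or assessor manual, and an article need not repeat it. This stands against any claim that the data must be empty, and the missing code alone would be no finding. It does not rescue the model: step 4 takes exactly that reading and still finds a floor-bound baseline and a mixture at later visits.

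It also stands that inability at stage I-III is inferred from one-line stage definitions. The article gives no completion rates, does not say which hand is tested, and admits FMA-UE scores up to 46 of 66. The FMA-UE ceiling does not widen entry, though, because the Brunnstrom limit applies as well. Some patients may become scorable at later visits. Nor is an ANOVA on scores with a floor worthless, since a difference in means can still be tested.

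A reader might infer more: that the plan would compare only patients who recovered, and that this selection would hide or reverse a benefit. The documents do not support that. No completers-only comparison is planned. It also conflicts with listwise deletion, which would drop recovered patients who had no baseline time. Under the model in step 4, a completers-only difference would shrink from 1.13 SD to 0.32, 0.43 or 0.57 SD at the three thresholds. It would not change sign. Those figures rest on assumed thresholds and a borrowed effect size, and they describe an analysis the trial has not proposed.

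**Conclusion.** The point holds for baseline and for the choice of model. By the protocol's own definitions, nearly all enrolled patients are likely to be unscorable or at floor on the 9HPT before treatment. The stated ANOVA works badly under either coding of inability: few patients if it is missing, a near-constant baseline and a mixed distribution later if it is zero.

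The size cannot be fixed from the documents. It depends on the share able at each visit, which is assumed throughout the working. That almost no data would be scorable at later visits is not established.

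The 9HPT is one of several secondary outcomes, and the FMA-UE result is unaffected. The change should be made, but it does not threaten the trial's main conclusion.

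**What to change.** Take the 9HPT out of the four-level ANOVA and replace it with wording along these lines:

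> The 9HPT will be scored as pegs per second, higher being better, with 0 for a patient who attempts the test and cannot complete it. All randomised patients will be compared between arms at 4 weeks and at follow-up by (a) the proportion able to complete the test and (b) a rank-sum test in which patients unable to complete it share the worst rank.

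If time in seconds is kept instead, the worst-rank rule serves the same purpose, and the direction of the score must then be stated. The record should separate a test attempted and failed from a visit not attended, so that inability is not handled as missing data.

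This changes analysis wording and needs no new measurement. The small downside is that the result is a proportion and a rank comparison, not a difference in seconds.

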### Imaging outcome measures

Subjects will undergo Rs-fMRI scans utilizing a gradient echo EPI sequence (repetition time = 2000 ms, echo time = 30 ms, FOV = 220 × 220mm^2^, flip angle = 90°, matrix size = 64 × 64, 30 transverse slices, slice thickness = 4 mm, gap = 0.8 mm). Each Rs-fMRI acquisition will yield 240 volumes [36]. High-resolution T1-weighted 3D anatomical images will be obtained in the sagittal orientation using a fast field echo sequence, repetition time (TR) = 7.4 ms; echo time (TE) = 3.6 ms; flip angle = 8^◦^; field of view (FOV) = 250 × 250 mm^2^; matrix = 228 × 227; 150 slices; slice thickness = 1.1 mm with no gap and voxel size = 1.1 × 1.1 × 1.1 mm^3^. DTI parameters were a spin echobased echo-planar imaging sequence in contiguous axial planes that included 16 volumes with diffusion gradients applied along 15 noncollinear directions (*b* = 800 s/mm^2^) and one volume without diffusion weighting (*b* = 0 s/mm^2^). Each volume consisted of 65 contiguous axial slices covering the entire brain (TR = 6973 ms; TE = 75 ms; flip angle = 90^◦^; FOV = 224 × 224 mm^2^; matrix = 112 × 112 and voxel size = 2 × 2 × 2 mm^3^). All MRI scans need to be performed by a specialized imaging physician, with the patient being scanned for both fMRI and DTI sequences in a single session, with the fMRI scan taking approximately 15–20 min, followed by the DTI scan taking approximately 5–10 min. The DTI and fMRI scanning workflow diagram is shown in Fig. 4.

**Fig. 4 Fig4:**
[figure not shown]
The DTI and fMRI scanning workflow diagram

### Image data acquisition and preprocessing

For fiber tract identification, we will use automated fiber quantification (AFQ) software to identify 20 WM tracts in each participant’s brain [37]. The identification procedure included three primary steps: (1) whole-brain deterministic fiber tractography, (2) waypoint ROl-based tract segmentation, and (3) probability map-based fiber refinement. Twenty fiber tracts will be identified according to the predefined ROls and probability maps: bilateral thalamic radiation CST, cingulum cingulate, cingulum hippocampus callosum forceps major, callosum forceps minor, bilateral inferior front-occipital fasciculus (IFOF), bilateral inferior longitudinal fasciculus(lLF), superior longitudinal fasciculus (SLF), bilateral uncinate, bilateral arcuate. Then, each fiber bundle will be divided into 100 segments. Finally, the FA, MD, AD, and RD of each segment of each fiber bundle will be calculated. The automated calculation will be performed by MATLAB 2011b. First, the effective self-diffusion tensor will be computed from the movement and distortion-corrected dataset [38]. The unit-less FA is an anisotropy index and ranges from 0 in fully isotropic diffusion to 1 in fully anisotropic diffusion [39]. Mean FA will be calculated for the affected and unaffected sides of each patient within a 5-mm radius of the posterior limb of the internal capsule. For methods, see Radlinska et al. [40]. Based on this, the diffusion indicators of rFA and FAasy are calculated for both participant groups using the following formula:$$\begin{array}{l}rFA=\frac{F{A}_{ipsilesional}}{F{A}_{contralesional}}\\ F{A}_{asy}=\frac{F{A}_{contralesional}-F{A}_{ipsilesional}}{F{A}_{contralesional}+F{A}_{ipsilesional}}\end{array}$$

The values of rFA and FAasy ranged from 0 to 1. The lower the rFA and the higher the FAasy, the more significant the decrease in ipsilateral CST anisotropy of the lesion, i.e., the more severe the impairment of CST integrity.

### fMRI

The fMRI is an imaging technology without intervention and employs magnetic resonance for quantifying hemodynamic alterations triggered by neuronal activity, indicating brain region activation. On patient readiness, full brain scans commence during rest-state scanning, instructing them to unwind, occlude vision, and refrain from intentional cognitive tasks. Images of the patients with left‐sided lesions will be flipped before preprocessing. After flipping, the right hemisphere will be tagged as the ipsilesional side and the left hemisphere as the contralesional side. fMRI preprocessing will be carried out using DPARSF, which provides a pipeline workspace based on Statistical Parametric Mapping (SPM; Wellcome Trust Centre for Neuroimaging, London) [41]. First, volumes from each run will be realigned to their first volume to estimate motion artifacts. The head motion will be then corrected using a six‐parameter rigid body spatial transformation. Functional mean images will be obtained and co‐registered to the corresponding individual structural image before normalization to the standard Montreal Neurological Institute (MNI) template. Finally, images will be smoothed with an 8‐mm isotropic Gaussian kernel.

### Functional connectivity analysis

In this study, seed-based analysis will estimate brain region connectivity strengths by calculating correlation coefficients of each brain area’s time series. ROIs will be identified from brain areas differing between healthy and stroke patients with impaired hand function. Pearson correlations between ROIs and all brain voxel time series will be assessed, transforming them into normal distributions through Fisher’s *z* transformation. A whole-brain functional connectivity analysis, seeding on the abnormal brain area, will identify the post-mirror therapy functional connectivity differences between the control and experimental groups [36].

